## 9 Adverse events/ Serious adverse events

### 9.1 Adverse event (AE)

An AE is every unfavorable and unexpected event (including for example abnormal lab values), every symptom or every illness that occurs in a temporal context with the use of a drug, irregardless of whether a connection with the use of the drug is assumed or not. Especially every change in lab values or vital functions which occurs and requires discontinuation of the study application is to be considered an AE.

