## 5.3 Adverse events, risks, and stress for study participants

- Under unfavorable conditions syncopes can occur during therapy on the Erigo. Possible risks include the loss of consciousness, prolonged bradycardia or hypotonia. However, we must point out that these orthostatic syncopes which occur in extreme cases can also occur in the transitional phase between lying and upright positioning during wheelchair mobilization, which takes place anyway, and the alternative tilt-table therapy. Since the passive leg movement on the Erigo occurs at the same time as the increased backflow of venous blood to the heart, the risk of syncope is according to the latest study information less on the Erigo than on the tilt table [6]). The remaining risks correspond to those of a typical physiotherapeutic treatment and thus are identical to those in the study and the control group. They are not increased by participation in a study compared to the usual therapy.

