**Therapeutic consequences must be documented, for example drug treatment, exclusion from the study.**

An event is termed an “unexpected adverse event“ in connection with the tested medical product (MP) if its nature or severity does not agree with the known data on the safety and tolerance of the MP.

**Causality:** The following definitions are used to determine the connection between the use of a medical product (MP) and the AE:

- **Safe:** A reaction that follows within a reasonable temporal course after use of the test product, that follows a known or expected response pattern to the suspected test product, and disappears when removed or when the dosage is reduced and recurs with repeated exposure.
- **Probable:** A reaction that follows within a reasonable temporal course after use of the test product, that follows a known or expected response pattern to the suspected test product, and disappears when removed or when the dosage is reduced and cannot be explained by the known features of the patient’s clinical state.
- **Possible:** A reaction that follows within a reasonable temporal course after use of the test product, that follows a known or expected response pattern to the suspected test product, but which can be easily elicited by a number of other factors.
- **No connection:** A reaction for which there is sufficient information available to assume that there is no connection with the test product.
- **Unassessable:** It is not possible to assess a connection.

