### **9.3.2 Reporting and recording serious adverse events**

As soon as a severe AE is observed, even in the inclusion phase, the principal investigator writes an AE report. The report must clearly identify the principal investigator. The report must be dated and signed by the principal investigator. The report should also contain an evaluation of the causal connection between event and medical product.

Any interruption of the study participation is also to be immediately documented.

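### The safety section ties adverse events to a drug in a device trial, triggers serious-event reporting by severity, and leaves some expected events open to interpretation

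*Protocol*

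**What the plan says.** Section 9.1 of the protocol gives the definition in several limbs. The first is "An AE is every unfavorable and unexpected event". The others are "every symptom or every illness that occurs in a temporal context with the use of a drug", and they apply "irregardless of whether a connection with the use of the drug is assumed or not". A further sentence adds that "every change in lab values or vital functions which occurs and requires discontinuation of the study application is to be considered an AE".

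Section 9.2 defines a serious event by outcome: death, threat to life, hospital admission or a longer stay, lasting disability, and so on. Section 9.3.1 requires every adverse event to be documented and grades intensity as mild, moderate or severe. It asks for causality in relation to the drug, but also for the relationship to the study application. Its causality scale refers to a medical product. It calls an event unexpected "if its nature or severity does not agree with the known data on the safety and tolerance of the MP". Section 9.3.2 is headed as the section on serious events and begins "As soon as a severe AE is observed, even in the inclusion phase".

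Section 5.3 lists the known risks: "Under unfavorable conditions syncopes can occur during therapy on the Erigo", together with prolonged bradycardia and hypotonia. It adds that such syncopes can also occur on the tilt table.

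**The concern.** An adverse event definition has to say which exposure counts, which occurrences count, and which of them need urgent reporting. Here each of the three is worded in a way that does not fit the trial or another part of section 9. The exposure is a drug that nobody receives as study treatment. The urgent-report rule uses a different scale from the one that defines seriousness. Expectedness appears inside the definition although the main risks are known in advance.

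At stake are the timing of serious-event reports and the consistency with which circulatory events are classified. Sections 5.3 and 11.1.1 state that syncope is less likely on the Erigo. The source behind 5.3 is the study that section 3 describes as done in healthy persons. The patients here cannot communicate in structured conversation (11.1.1), so recorded safety data are needed to judge that statement in this population.

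**Working it through.** No arithmetic applies; the check sets the sections side by side.

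**Step 1, exposure.** Section 9.1 and one sentence of 9.3.1 say drug. Another sentence of 9.3.1 says study application, and the causality scale says medical product. Sections 11.2.3 and 12 state that the study procedures use approved medical devices; section 12 names the Erigo and the tilt table. The only drugs in the protocol are the concomitant ones in section 8. One safety section thus names its exposure in three ways, and the one used in the definition is not a study treatment.

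**Step 2, seriousness against severity.** Two constructed cases show the effect of the trigger in 9.3.2 as written.

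| Case | Serious by 9.2 | Intensity by 9.3.1 | Documented under 9.3.1 | Triggers 9.3.2 |
|---|---|---|---|---|
| Prolongs the hospital stay, moderate intensity | yes | moderate | yes | no |
| Meets no criterion of 9.2, severe intensity | no | severe | yes | yes |

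The trigger misses the first case and catches the second. In the first case the immediate report is lost, not the record.

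**Step 3, which circulatory events count.** For this step, read drug as study device.

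| Event | First limb (unfavourable and unexpected) | Symptom or illness | Discontinuation sentence | Result |
|---|---|---|---|---|
| Syncope | doubtful, named in 5.3 | yes | not needed | adverse event |
| Presyncope with symptoms, angle lowered | not needed | yes | not clearly met | adverse event |
| Bradycardia or hypotension that stops therapy (section 10) | doubtful, named in 5.3 | not needed | yes | adverse event |
| Symptom-free blood pressure fall, angle lowered (section 10) | doubtful, hypotonia named in 5.3 | not clearly | not clearly, therapy goes on | open |

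Only the last row is unresolved. It turns on whether *unexpected* in 9.1 carries the meaning that 9.3.1 gives to an unexpected adverse event.

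**Step 4, other routes of capture.** Syncope has a planned analysis in the pilot study (6.2.1). In the randomized trial it is neither a listed outcome (4.2.2) nor a row in the schedule (7.5), so adverse event reporting is its main route there. Blood pressure is measured during sessions in both parts (7.1, 7.4, 7.5). The readings therefore exist even where the classification is open.

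**The case against.** The strongest reply is that nothing important is lost. The symptom and illness limbs carry no expectedness condition, only a temporal link is needed, and every adverse event is documented at any intensity. Severe under a heading about serious events is most naturally a slip; 9.3.1 even lists severity and intensity as separate items. Most of this stands, and it rules out several stronger readings that a reader might infer:

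- *That syncope and hypotension need not be recorded.* The first limb read alone suggests this, but the rest of 9.1 and the documentation rule in 9.3.1 contradict it.
- *That serious events of lesser intensity go unreported.* They are documented under 9.3.1; only the prompt for an immediate report is missing.
- *That tilt-table events have no causality assessment.* The relationship to the study application is requested, and section 12 lists the tilt table among the medical products. The wording is unclear, but a route exists.
- *That events are lost unevenly between arms.* Section 4.2.2 does expect a blood pressure drop on the tilt table, so differing classification is conceivable. But the definition is the same for both arms, and no rule in the protocol produces a difference.
- *That 450 to 600 sessions are affected.* With 50 patients, 9 monitored sessions (7.5) give 50 × 9 = 450, and four sessions a week for three weeks (section 6) give 50 × 12 = 600. That is exposure, not a count of lost events.

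Section 4.2 also says that the randomized trial collects the same parameters as the pilot. That might be taken to include syncope, but neither 4.2.2 nor 7.5 names it.

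The reply does not remove the faults. It works by reading drug as device and severe as serious, which is the correction that the text needs.

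**Conclusion.** The point holds as three wording faults in rules that staff must apply. Two are plain errors: the drug exposure in 9.1 and 9.3.1, and the severe trigger in 9.3.2. The third is an ambiguity, limited to expected, symptom-free blood pressure falls that lead only to a lower angle. It matters somewhat more because syncope in the randomized trial also relies on the adverse event route.

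The consequences are a possible delay in reporting serious events of mild or moderate intensity, and classification that depends on the reader. The number of events cannot be derived from the protocol. The conclusion assumes that 9.3.2 is meant to implement 9.2, as its heading indicates, and that the protocol text is what site staff work from. The correction is more than clerical, because it changes when serious events are reported and which events count. It is not evidence of a general failure to record safety events.

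**What to change.** Four edits to section 9:

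1. In 9.1 and 9.3.1, replace drug with *study device (Erigo or tilt table) or study procedure*.
2. In 9.1, delete *unexpected*, so that expected events count in both arms; keep the separate definition of an unexpected adverse event in 9.3.1.
3. In 9.3.1, state that causality is judged for whichever of the two devices the patient was treated on.
4. In 9.3.2, replace severe AE with *serious AE as defined in 9.2*.

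The clinical thresholds and actions in section 10 stay as they are. The cost is amendment wording and a few more adverse event entries, mainly for known orthostatic events.

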### 9.2 Serious adverse event (SAE)

Serious AEs (SAEs) are defined according to *The Trial Investigator`s GCP Handbook 1997* as any untoward medical occurrences that:

- result in death,
- are life threatening (the participant must be at immediate risk of death from the event as it occurred; this definition does not include a reaction that, if it had occurred in a more serious form, might have caused death),

- require (or prolong) hospitalization,
- cause persistent or significant disability/incapacity,
- result in congenital anomalies or birth defects,
- lead to other conditions that in the judgement of the investigators represent significant hazards.

### 9.3 Recording and reporting

#### 9.3.1 Recording an AE

Every AE must be documented in the report of adverse events.

In all cases the principal investigator must be clearly identified in the AE report. The report must be dated and signed by him/her. The report should moreover contain an evaluation of the causal connection between the event and the drug. The report form must be completed

The description of the AE includes the time of its occurrence, the duration, severity, intensity, outcome and the relationship to the study application and the necessary treatment. The principal investigator should estimate the intensity of every AE on the basis of the following classification:

- **Mild:** the symptom is clinically visible but the participant does not require treatment or intervention, and the symptom does not affect the participant's clinical status.
- **Moderate:** the participant is symptomatic and requires treatment because the symptom affects his/her clinical status.
- **Severe:** the participant is symptomatic and requires intensive treatment because the symptom significantly diminishes his/her clinical status.

**Therapeutic consequences must be documented, for example drug treatment, exclusion from the study.**

An event is termed an “unexpected adverse event“ in connection with the tested medical product (MP) if its nature or severity does not agree with the known data on the safety and tolerance of the MP.

**Causality:** The following definitions are used to determine the connection between the use of a medical product (MP) and the AE:

- **Safe:** A reaction that follows within a reasonable temporal course after use of the test product, that follows a known or expected response pattern to the suspected test product, and disappears when removed or when the dosage is reduced and recurs with repeated exposure.
- **Probable:** A reaction that follows within a reasonable temporal course after use of the test product, that follows a known or expected response pattern to the suspected test product, and disappears when removed or when the dosage is reduced and cannot be explained by the known features of the patient’s clinical state.
- **Possible:** A reaction that follows within a reasonable temporal course after use of the test product, that follows a known or expected response pattern to the suspected test product, but which can be easily elicited by a number of other factors.
- **No connection:** A reaction for which there is sufficient information available to assume that there is no connection with the test product.
- **Unassessable:** It is not possible to assess a connection.

### **9.3.2 Reporting and recording serious adverse events**

As soon as a severe AE is observed, even in the inclusion phase, the principal investigator writes an AE report. The report must clearly identify the principal investigator. The report must be dated and signed by the principal investigator. The report should also contain an evaluation of the causal connection between event and medical product.

Any interruption of the study participation is also to be immediately documented.

### **9.4 Procedure during and after the study**

The principal investigator monitors the development of undesired clinical events or unhealthy lab values until the condition of the study participant improves or stabilizes.

## **10 Termination criteria**

Individual

- If the systolic blood pressure falls by 20 mmHg or the diastolic blood pressure by more than 10 mmHg during the uprighting of the patient, therapy is continued at the next lowest tolerated angle of uprightness (30 or 50 degrees).
- The same procedure is followed with symptoms of a presyncope (tachypnoe, paleness, increased sweating...).
- Therapy is immediately terminated if the pulse falls below 40 beats/min or rises above 140 beats/min.
- Arterial hypotension (<80 mmHg).
- The occurrence of a new disease or complication of the primary illness that makes a continuation of the study impossible.
- Legal proxy withdraws participation agreement.

## **11 Ethical and legal regulations**

### **11.1 Ethical regulations**

The study will be conducted according to the Declaration of Helsinki and the ICH-GCP guidelines.

Participation in this study is voluntary. The legal proxy can withdraw his/her agreement to participate in the study at any time for any reason without affecting his/her dependent. If a legal proxy chooses that the patient not be in this study, it will not affect the right of the patient to any current or future medical care to which he/she is entitled.

#### **11.1.1 Informed consent form**

The study aim is to investigate tilt table/Erigo treatment of patients in the vegetative or minimally conscious state. These patients are not able to communicate in any structured conversation. Thus the study involves only patients who require legal care, except in case a medical care power of attorney is possessed

In the context of this study only therapeutic procedures or a combination thereof are used (verticalization and passive movement), which have been applied for centuries in early neurological rehabilitation. Although the data on these procedures from controlled clinical studies as regards the efficacy are insufficient, it is our opinion that withholding the stimulation methods from these patients – i.e., not applying them – is ethically questionable. Moreover, the risk of syncope as undesired effects in the new therapy on the Erigo – presented above – is less than in the classic tilt-table therapy. All in all, a constancy or improvement of efficacy or reduction of risk is to be expected with the Erigo in comparison with the established tilt-table therapy.

Before enrollment the patient's legal proxy will be informed verbally and in written form about the nature and character of the study, especially about its risks and benefits. Consent to participate will be given in written form by signing the informed consent form.

## **11.2 Legal regulations: Abidance by the law**

This means that the regulations of the medical devices act (MDA) will be observed and the "Basic principles of the proper performance of the clinical trial of drugs" as well as the Federal Data Protection Act (FDPA) will be applied.

### **11.2.1 Obligatory registration of the study**

According to § 17 MPG (Medizinproduktegesetz, Medical Devices Act) this study will be registered with the relevant State Authority.

### **11.2.2 Permission of the Ethics Committee**

The trial protocol will be approved by the Ethics Committee of the Bavarian State Chamber of Physicians before the start of the study. The study will not begin without the written permission of the Ethics Committee.

### **11.2.3 Patient insurance**

The medical devices will be applied in accordance with their intended use. A separate insurance for the study patients is not necessary, as only approved medical devices will be used for all study procedures. In addition, all study procedures are non-invasive. In comparison with the standard rehabilitation interventions no additional risks are expected to result from study participation.

The Neurologische Klinik Bad Aibling has a third party liability insurance for residence purposes (insurance company: Bayerischer Versicherungsverband, [name], Versicherungsschein-Nr.: HV 77281 0500). This insurance covers all diagnostic and therapeutic interventions. The sum insured for personal injuries amounts to €5,200,000.

### **11.2.4 Data safety/ Confidentiality**

The personal and other confidential information of patients are subject to the medical confidentiality and regulations of the Bundesdatenschutzgesetzes (Federal Data Protection Act). Any disclosure of patient data if necessary takes place only in anonymized form. If it is necessary in the course of the study to identify the name of a patient (monitoring), this is possible since the patients have expressed in writing their agreement that the principal investigator may be relieved of his nondisclosure obligation so that federal health officials can inspect the original patient files in order to check that the study is being properly conducted.

## **12 List of medical products**

The Erigo used in the therapy is from the firm Hocoma; this is an approved medical device for use in the approved function (CE 0124). The tilt table and all medical devices for the above-planned examinations will be only medical devices that are used in their approved function, which is applied in the usual clinical operations of the Neurological Klinik Bad Aibling.

